### Outcome measures

#### Data collection sheet

A purposefully designed questionnaire consisting of two sections will be used to collect demographics (including age, country of birth, ethnic background, weight, height, BMI, number of previous vaginal births and/or caesarean sections, number of previous miscarriages, abortion and stillbirth, family history of keloid scars, history of any previous surgery and keloid scar on another site of body, gestational age at the time of baseline assessment) and any prior treatment of the keloid scar (section 1) and data on the keloid scar (section 2) including redness, hardness and elevation of the scar compared to the surrounding skin (0 = none, 1 = partially, 2 = entire scar). This section of the questionnaire also enquires about subjective symptoms of the scar including, but not limited to, itching, pain and swelling (0 = none, 1 = occasionally, 2 = all the time). The scar will be measured in millimetres using a hardened stainless steel 150mm Digital Vernier Caliper (Kincrome Pty Ltd, Scoresby, Australia) with a liquid-crystal display (LCD) screen to read an accurate measure to the nearest 0.02 mm. We will also take photographs of the scar to compare the visual changes. Section 2 of the questionnaire will be used at follow-up visits to collect data on the changes in the keloid scar. The same 150mm Digital Vernier Caliper will be used at follow-up visits, and the scars will be photographed again. To improve the objective validity of the trial and minimise recall bias of patients in the symptom scores, the participants will be shown photographs of the scar both before and one year after the intervention. They will be asked if they see any improvement before and after participating in the trial, both before and after seeing their scar photographs. In addition, the participants will assess and grade their satisfaction with the treatment on a 4-point scale (0 = no improvement/poor, 1 = fair, 2 = good, 3 = excellent). The participants will be queried on their overall satisfaction with the treatment (5 = very satisfied, 4 = slightly satisfied, 3 = neutral satisfaction, 2 = slightly unsatisfied, 1 = very unsatisfied). They will also be asked if they think they were in the intervention arm or the control arm of the trial before revealing this information to them at the final visit.

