### Blinding

The participants receiving the treatment, the researcher assessing the outcomes and the statistician analysing the data will be blinded to the intervention allocation. The nature of the study is such that the surgeon cannot be blinded to the type of intervention.

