### Randomisation

Through a parallel intervention assignment, the independent researcher will use a computer-Vgenerated random-numbers list to determine group allocation. The researcher will then place each allocation into sequentially numbered opaque envelopes. There will be permuted blocks of 10 with 1:1 allocation, containing 5 intervention and 5 control allocations in each block. This will help achieve balance across the two groups.

For those who are randomised to triamcinolone acetonide, the independent researcher will insert the medication inside the envelope and, after sealing it, will store the envelope in a locked cabinet inside the medication room in the birth unit. The surgeon who is rostered on the day of the caesarean section will be informed of the recruited participant and will be instructed on where to collect the concealed envelope. All participants will have their randomisation number indicated in the hospital electronic record at the time of study allocation. This is done to inform the researcher assessing the outcomes of the recruiting of the participant and the allocated number, but not the allocated intervention.

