### Follow-up

The follow-up period consists of 12 months face-to-face visits (Fig. 1). Post-operation, the patients will be visited daily on the ward for any signs of potential infectious local complications of the treatment and immediate side effects of the medication injection until the discharge home. The patients will then be visited in the women’s health clinic at the hospital for their 6th week post-partum check. The next follow-up times will be 6 months and 12 months post caesarean section. At each follow-up visit, the same assessment and scoring scales will be used to evaluate the changes to the keloid scar. Late side effects of the medication injection as well as symptoms of depression, anxiety and stress, and participants’ satisfaction will be assessed during follow-up visits at 6 weeks, 6 months and 12 months post-partum. The participants will also be asked if they would recommend such a procedure to another woman with a caesarean section keloid scar (yes/no) and if they would repeat the experience again in a future pregnancy (yes/no).

All measurements at baseline and follow-up visits will be performed by the same researcher, who will also make all efforts to ensure compliance with follow-up. As part of continuous clinical care, patients with any residue keloid scar with be given information on further treatment including referral to plastic surgeons if they are interested (Fig. 2).

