### Trial status

The present protocol is version number 4, dated October 2018. The recruitment began in May 2019 and is expected to complete by June 2021.

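### Allocation is disclosed at each woman's own 12-month visit, not after the last one, which puts the sole assessor's blinding at avoidable risk for women graded later

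*Protocol article*

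**What the plan says.** **Disclosure.** The Data collection sheet section has each woman state which arm she believes she was in "before revealing this information to them at the final visit". The Follow-up section makes that visit individual to her: "The follow-up period consists of 12 months face-to-face visits", and "The next follow-up times will be 6 months and 12 months post caesarean section".

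**Assessor.** Follow-up also states: "All measurements at baseline and follow-up visits will be performed by the same researcher". The Blinding section says that "the researcher assessing the outcomes and the statistician analysing the data will be blinded to the intervention allocation", without an end date or exception.

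**What the assessor knows.** Under Randomisation, each woman's randomisation number goes into the hospital electronic record: "This is done to inform the researcher assessing the outcomes of the recruiting of the participant and the allocated number". The arm is withheld. The same section fixes the list: "There will be permuted blocks of 10 with 1:1 allocation, containing 5 intervention and 5 control allocations in each block". The envelopes are numbered in sequence.

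**Calendar.** Trial status reports: "The recruitment began in May 2019 and is expected to complete by June 2021". The 12-month visits are therefore spread over about two years.

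**The concern.** Each of these rules is reasonable alone. Together they leave a gap. Allocations start to be released while nearly all 12-month outcomes are still to be measured, at visits where a single person does all the measuring. If that person learns the released allocations, the numbers and fixed blocks allow inference about women in the same block who have not yet had their final grading.

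At stake are the items this researcher grades by eye and touch on a 0 to 2 scale: elevation, hardness and erythema. They feed the second component of the primary outcome (change in appearance and specification). The surgeon cannot be blinded, so blinded grading is a main protection for that comparison. An assessor who knows or suspects the arm could tilt the grades, plausibly towards the injection. The documents give no basis for putting a size on that bias.

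**Working it through.** The plan gives no figure of its own on this point. The inputs are 150 women (Sample size), fixed blocks of 10 with 5 per arm (Randomisation), recruitment from May 2019 to June 2021 (Trial status) and a final visit 12 months after the caesarean (Follow-up).

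**1. When disclosure starts**

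Assumptions: uniform accrual over T = 24 to 26 months, depending on the days of the month, and about 1 month from randomisation (around 36 weeks) to the caesarean. The first disclosure then falls at month 1 + 12 = 13.

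| Quantity | Formula | T = 24 | T = 26 |
|---|---|---|---|
| Enrolled at first disclosure | 150 × 13/T | 81 | 75 |
| 6-month visits done by then | 150 × (13 − 7)/T | 37.5 | 34.6 |
| 12-month visits done when accrual ends | 150 × (T − 13)/T | 69 | 75 |

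At the first disclosure, 149 of 150 twelve-month assessments and about 112 to 115 six-month assessments are outstanding. When accrual ends, at least half of the 12-month assessments remain. These numbers count pending visits, not compromised ones.

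**2. Which gradings could be affected through the blocks**

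At 150/26 = 5.8 women a month, a block of 10 fills in about 10/5.8 = 1.7 months. The last woman in a block reaches her 6-month visit well before the first woman in that block reaches 12 months. Inference within a block therefore bears on the 12-month grading and not on the earlier ones.

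**3. Allocations deducible with certainty**

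Once all 5 allocations of one arm in a block are known, the rest of that block is known. With m = 5 per arm, the expected number left at that point is 2m/(m + 1) = 10/6 = 1.67 per block. With 150/10 = 15 blocks, 15 × 1.67 = 25 of 150 (16.7%).

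**4. Best guess overall**

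Always guessing the arm with more places left in the block (Blackwell–Hodges), the expected number correct per block is

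5 + (2^10/C(10,5) − 1)/2 = 5 + (1024/252 − 1)/2 = 6.53 of 10, or 65.3% against 50%.

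This includes the certain cases. Among the others the rate is (6.53 − 1.67)/(10 − 1.67) = 4.86/8.33, about 58%.

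**5. Sensitivity to visit order**

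Positions within a permuted block are exchangeable, so the results hold for any visit order unrelated to arm. Simulating 15 blocks gave 25.0 of 150 and 65.3%; with visit dates moved by up to 30 days either way, 25.1 and 65.3%.

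**6. Conditions behind steps 3 and 4**

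The assessor hears every disclosure, the randomisation number gives the place in the list, the assessor knows and uses the block size, and every block is complete with every final visit attended. If any of these fails, the figures fall.

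**The case against.** The strongest objection is that the text never says the assessor learns an allocation. The information is revealed to the participants, by a person not named. An independent researcher holds the list, and the Randomisation section withholds the arm from the assessor. If someone else discloses, out of the assessor's hearing, all the passages agree. Who discloses, and in what order within the visit, is also operating detail that an article may leave to the full protocol.

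This stands, and it rules out three stronger readings that a reader might infer:

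- **That the assessor is progressively unblinded.** The documents do not show it; they only state no step that prevents it.
- **That the disclosure rule flatly contradicts the Blinding section.** It does so only if the assessor discloses or overhears.
- **That up to 149 of 150 assessments are compromised.** Knowing one woman's arm determines nothing about women in other blocks. Even in the upper-end case, 150 − 25 = 125 are never known with certainty.

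The identity of the discloser does matter. No trial assessment is scheduled after the final visit, so what a woman knows from then on affects none of her own data. The listing in the Data collection sheet section also suggests, without fixing it, that her measurements come before her disclosure.

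Exposure also differs by outcome. Caliper length and width, photographs, and the patient's own scores for itching, pain and swelling are less open to an assessor's expectation. The article does not say who judges keloid formation.

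What the objection does not remove is the timing. That is a stated rule and not a missing detail. It makes the sole assessor's blinding depend on every final visit being handled without a slip while most final gradings are pending.

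**Conclusion.** The point holds as a risk created by the timing of disclosure; actual unblinding is not established. The upper-end size is about 25 of 150 allocations certain before the 12-month grading and best guesses right 65.3% of the time, under the conditions in step 6. If the assessor hears nothing, carry-over by this route is nil. The items at risk are mainly the 12-month grades for elevation, hardness and erythema.

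A second route cannot be quantified. The Discussion lists atrophy, telangiectasia and hypopigmentation as common effects of the drug, and an assessor who learned the arms of earlier women could match such signs to allocation in later ones.

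Sample size and power are not affected. This is a cheap improvement, not a flaw that invalidates the design.

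**What to change.** - Keep the guess-the-arm question at the 12-month visit.
- Disclose allocation only after the last woman's 12-month assessment is complete and the database is locked, through the independent researcher and not the assessor, for example by letter.
- Give the assessor a study ID that does not follow the randomisation sequence. This is a supplement only: the same researcher takes the baseline measurements and will know the rough order of entry, so the deferral does the main work.
- If an individual woman needs to know earlier, for instance in connection with the further care offered under Follow-up and Ancillary and post-trial care, someone other than the assessor should tell her by a separate route.

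With the deferral, the number of allocations deducible through these disclosures before assessment is 0 of 150. The cost is a sentence or two of protocol text and a mail-out. The downside falls on early participants: the first woman waits about as long as accrual lasts, 24 to 26 months beyond her own final visit.

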#### Depression, Anxiety and Stress Scale-21 (DASS-21)

The DASS-21 is the short version of the DASS-42 questionnaire. It contains a set of three self-report scales and will be used to measure anxiety, depression and stress during pregnancy and after childbirth. The DASS-21 has been shown to have high internal consistency and to yield meaningful discriminations in a variety of settings. It should meet the needs of both researchers and clinicians who wish to measure current state or change in state over time on the three dimensions of depression, anxiety and stress. The tool has been used in previous studies on perinatal women in Australia, Canada, Chile, England, Germany, Iceland, New Zealand and the USA with reasonable response rates [14, 15]. Each of the three DASS-21 scales contains 7 items. The Depression scale assesses dysphoria, hopelessness, devaluation of life, self-deprecation, lack of interest/involvement, anhedonia and inertia. The Anxiety scale assesses autonomic arousal, skeletal muscle effects, situational anxiety and subjective experience of anxious affect. The Stress scale is sensitive to levels of chronic non-specific arousal. It assesses difficulty relaxing, nervous arousal and being easily upset/agitated, irritable/over-reactive and impatient. Respondents are asked to use 4-point severity/frequency scales to rate the extent to which they have experienced each state over the past week. Scores for Depression, Anxiety and Stress are calculated by summing the scores for the relevant items and then multiplying each scale score by 2. Then, each score can be transferred to the DASS profile sheet, enabling comparisons to be made between the three scales and also giving percentile rankings and severity labels as shown in the following table.

**Table Taba:** 

	Depression	Anxiety	Stress
Normal	0–9	0–7	0–14
Mild	10–13	8–9	15–18
Moderate	14–20	10–14	19–25
Severe	21–27	15–19	26–33
Extremely severe	28+	20+	34+

#### Post-operation survey for the surgeon

After the participant has had her caesarean section, the surgeon will complete a questionnaire. In both arms, the surgeon will be asked if the keloid scar was completely excised, and any difficulty of the ascribed surgical technique will be noted. In the intervention arm, the surgeon will also note any difficulty with sub-dermal injection of triamcinolone acetonide, any spill of the medication out of the wound and whether the needle punctured the skin when injecting with triamcinolone acetonide. A diagram is given to indicate the area of anticipated problems if any.

### Blinding

The participants receiving the treatment, the researcher assessing the outcomes and the statistician analysing the data will be blinded to the intervention allocation. The nature of the study is such that the surgeon cannot be blinded to the type of intervention.

### Allocation concealment

Allocation concealment will be used to prevent selection bias by concealing the allocation sequence. This will be done by an independent researcher who works neither in the operating theatre nor in the clinic. This will prevent the researcher from influencing which participants are assigned to a given intervention group and reporting bias.

### Randomisation

Through a parallel intervention assignment, the independent researcher will use a computer-Vgenerated random-numbers list to determine group allocation. The researcher will then place each allocation into sequentially numbered opaque envelopes. There will be permuted blocks of 10 with 1:1 allocation, containing 5 intervention and 5 control allocations in each block. This will help achieve balance across the two groups.

For those who are randomised to triamcinolone acetonide, the independent researcher will insert the medication inside the envelope and, after sealing it, will store the envelope in a locked cabinet inside the medication room in the birth unit. The surgeon who is rostered on the day of the caesarean section will be informed of the recruited participant and will be instructed on where to collect the concealed envelope. All participants will have their randomisation number indicated in the hospital electronic record at the time of study allocation. This is done to inform the researcher assessing the outcomes of the recruiting of the participant and the allocated number, but not the allocated intervention.

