### Sample size

Using the estimates from the study by Khalid et al. [13], the intervention will increase the incidence of efficacy of treatment for keloid scarring from 45% in the excision followed by radiation group to 70% in the excision followed by intralesional triamcinolone acetonide and 5-fluorouracil group. We calculated that a total of 150 patients (75 in each group) would provide 80% power with a two-sided significance level of 5% to detect this difference between the groups. This allows for 10% non-compliance.

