### Procedures

All eligible women will be approached at the time of booking into the clinic for caesarean section at around 36 weeks and will be given information about the study. Those women who meet the inclusion criteria and sign the informed consent form will be randomised to either the intervention or the control group by the independent researcher as explained previously (Fig. 1). On the day of the caesarean section, the sealed envelope containing instructions for the type of treatment will be picked up by the surgeon. The surgeon opens the envelope when the woman is ready for the caesarean section.

The control group will receive surgical excision of the keloid scar at the beginning of the procedure during skin incision. The baby will be delivered as normal, and routine wound closure will be performed in accordance with National Institute for Health and Care Excellence (NICE) guidelines as follows: The uterus is closed in two layers followed by closure of the rectus sheath, all using continuous sutures with 1-Vicryl (Johnson & Johnson). The fat layer is closed with interrupted plain gut sutures 2 cm apart. The skin layer is then closed with 3-0 Monocryl (Ethicon) in a sub-cuticular fashion.

The intervention group will receive surgical excision of the keloid scar after the delivery of the baby. Closure of the uterus layers, rectus sheath and the fat layer are completed as explained above. Then, triamcinolone acetone will be injected sub-dermally at the time of wound closure. Two ampules of triamcinolone acetonide (Kenacort®-A 10 suspension, Aspen Pharma Pty Ltd) will be administered at a single dose; each ampule contains 10 mg/1 ml active medication. The surgeon will inject one ampule along the entire length of the upper edge of the skin incision and one ampule along the entire length of the lower edge of the skin incision, using a 25 G needle.

After the procedure is completed, the surgeon will fill in the post-operation survey. The excision of the scar and administration of the injection will be performed by the surgeon who is scheduled to perform the surgery on that day. All the surgeons in the Department of Women’s and Newborn Health will be trained on how to perform the excision and injection of the triamcinolone. The Principal Investigator of the study will assess the fidelity to the intervention by supervising procedures.

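### One fixed, published block size of 10 makes some late-block assignments predictable to anyone following nearly all procedures: a modest, avoidable risk

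*Protocol article*

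**What the plan says.** The Randomisation section of the protocol article fixes the scheme: "There will be permuted blocks of 10 with 1:1 allocation, containing 5 intervention and 5 control allocations in each block". No strata and no variation in block size are mentioned, and Setting names a single hospital. Envelopes are opaque and sequentially numbered. The same section adds: "All participants will have their randomisation number indicated in the hospital electronic record at the time of study allocation". The stated purpose is to give the outcome assessor the number but not the arm.

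Three groups learn arms, or may learn them, while the trial runs:

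- Surgeons. Blinding says: "The nature of the study is such that the surgeon cannot be blinded to the type of intervention".
- The Principal Investigator. Procedures says: "The Principal Investigator of the study will assess the fidelity to the intervention by supervising procedures". The share of procedures supervised is not given.
- Whoever is present when a participant is told her arm at the final visit (Outcome measures, Data collection sheet).

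There are safeguards. Under Allocation concealment, an independent researcher who works in neither theatre nor clinic handles the sequence. Under Procedures, women are approached and randomised at around 36 weeks, and the surgeon opens the envelope only when the woman is ready for the operation.

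**The concern.** In a block known to hold five of each arm, the rest is determined once five of one arm have been seen. Before that, the running imbalance shifts the odds. If the recorded number shows where a block starts and ends, the published size is all that an informed observer needs.

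Two things are at stake. The first is entry to the trial. If someone with influence over who is approached or accepted could foresee the arm, the women entering the two arms could differ, and intention-to-treat analysis does not repair that. The second is blinded assessment. One researcher makes all measurements (Follow-up), grades elevation, hardness and erythema on a 3-point scale, and holds the randomisation numbers. If that researcher learned arms as they were revealed at 12 months, the fixed block would disclose the arms of some women in the same block still awaiting their final assessment.

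**Working it through.** **Plan's own figure.** Sample size gives "a total of 150 patients (75 in each group") for an increase "from 45% in the excision followed by radiation group to 70% in the excision" group of the comparison it cites, at 80% power and two-sided 5%, and adds: "This allows for 10% non-compliance". The pooled-variance formula gives (1.96·√(2·0.575·0.425) + 0.8416·√(0.45·0.55 + 0.70·0.30))² / 0.25² = 60.2. The continuity correction raises this to 68 per arm, and 68 × 1.1 = 74.8, so 75 per arm and 150 in total. The figure reproduces. It matters here only because 150 is exactly 15 complete blocks of 10.

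**Ceiling: every earlier arm in the block known at once.** After s allocations have been seen, the chance that the next is certain is 2·C(5, s−5)/C(10, s) for s = 5 to 9, and 0 for smaller s.

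| Position in block | Allocations seen | Chance that it is certain |
|---|---|---|
| 1–5 | 0–4 | 0 |
| 6 | 5 | 2/252 = 0.8% |
| 7 | 6 | 10/210 = 4.8% |
| 8 | 7 | 20/120 = 16.7% |
| 9 | 8 | 20/45 = 44.4% |
| 10 | 9 | 100% |

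The sum is 1.667 per block (= 10/6), and 15 × 1.667 = 25 of 150. The expected number of correct best guesses per block is 5 + 2⁹/C(10,5) − 0.5 = 5 + 2.032 − 0.5 = 6.53 of 10, or 65.3%.

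**At consent: the most recent envelopes are still sealed.** With L sealed, each position draws on L fewer known arms, so the L largest chances in the table drop out of the sum.

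| Sealed at enrolment | Certain, of 150 | Best guess right |
|---|---|---|
| 0 | 25 | 65.3% |
| 1 | 10 | 60.3% |
| 2 | 3.3 | 58.1% |
| 3 | 0.8 | 55.9% |
| 4 | 0.1 | 54.4% |
| 5 | 0 | 53.0% |

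Trial status gives recruitment from May 2019 to June 2021, about 25 months, so 150/25 = 6 women per month, or 6 × 12/52 = 1.38 per week. The interval from randomisation to surgery is not stated. An assumed one to four weeks leaves about 1.4 to 5.5 envelopes sealed, and three weeks leaves about 4.

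**Partial observation, no lag (simulated).** Someone seeing 75% of procedures is certain of 5.9 of 150, someone seeing 50% of 0.8, and someone seeing 25% of almost none.

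**Effect of varying the size (simulated).** The observer is assumed to see every arm at once and to know the set of sizes, but not where blocks end. Certain assignments fall from 25 of 150 to about 3.5 with sizes 4/6/8, 2.5 with 6/8/10 and 1.2 with 4/6/8/10/12. With one envelope sealed they fall from 10 to about 1–2. The best-guess rate with no lag stays at 66–68%, against 65%.

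**The case against.** A reader might infer that the people who recruit can work out the next arm and select women accordingly. The article does not support this. It nowhere says that surgeons or the Principal Investigator approach, screen or consent women. Operations go to whichever surgeon is rostered, so one surgeon sees only part of a block. The arm is disclosed only at surgery, after consent. The article also does not state that the recorded randomisation number equals the envelope's sequence number. At the planned rate and an assumed three-week interval, certainty at consent is close to nil. Blocks of 10 in an unstratified single-site trial are a defensible choice. All of this stands, and it limits the size of the risk.

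It does not remove the risk. The interval is unstated, and slower recruitment or a shorter interval leaves fewer envelopes sealed. The lag also protects only if sealed envelopes reveal nothing; the Randomisation section describes medication being placed in the triamcinolone envelopes, which is a separate concealment question. The final-visit route does not depend on the enrolment lag at all, although the article does not say who reveals the arm.

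A second tempting step is to abandon blocks for a single random 75:75 list. With no lag that looks better (54.8% best guess). With four envelopes sealed it gains almost nothing (54.0% against 54.4%), and with five it is more predictable than blocks of 10 (53.9% against 53.0%). It could also unbalance the interim look at 20 patients. Two full blocks give 10:10, whereas the single list gives 10:10 with probability 19% and a split of 7:13 or worse with probability 23%.

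**Conclusion.** The point holds as a minor design weakness, not as a demonstrated bias. The fixed, published block lets an observer with complete and immediate knowledge be certain of at most 25 of 150 assignments. At consent the figure is 10, 3.3 or 0.1 of 150 with 1, 2 or 4 envelopes sealed, and about 4 sealed is the central expectation under the assumed three weeks and the planned 6 women per month. These figures assume that block position can be read from the recorded number and that the observer follows essentially every procedure; seeing half of them leaves less than one certain assignment. The sample size and the planned analysis are unaffected.

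**What to change.** In the Randomisation section, have the independent researcher vary the block sizes at random, including sizes of 10 or more, for the unused part of the list. State only that sizes vary. Keep the sizes and the list with that researcher until the last outcome is recorded. In the hospital record, use a study number that does not show block position.

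The cost is a sentence or two of text, a re-run of the unused list and, because recruitment has begun, remaking the unused envelopes. Arm counts may be slightly less even at the look at 20 patients or if recruitment stops mid-block. The gain should not be oversold: the change removes most certain predictions, but guessing from the running imbalance remains about as good as before.

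### Only the intervention envelopes hold the drug, so the arm can probably be felt before the planned opening, which weakens concealment between randomisation and surgery

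*Protocol article*

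**What the plan says.** All references are to the protocol article.

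- **Allocation concealment** sets the aim: "Allocation concealment will be used to prevent selection bias by concealing the allocation sequence". The task belongs to an independent researcher who has no role in theatre or in the clinic.
- **Randomisation** describes the mechanism: "The researcher will then place each allocation into sequentially numbered opaque envelopes". It continues: "For those who are randomised to triamcinolone acetonide, the independent researcher will insert the medication inside the envelope". That envelope is then sealed and locked in a cabinet in the birth unit's medication room. The same section fixes the list: "There will be permuted blocks of 10 with 1:1 allocation".
- **Procedures** gives the drug as two ampules, of which "each ampule contains 10 mg/1 ml active medication". The control arm has no injection. Women are randomised after meeting the criteria and signing consent, at around 36 weeks. On the day of surgery "the sealed envelope containing instructions for the type of treatment will be picked up by the surgeon", and it is to be opened only once the woman is ready for the operation.
- **Blinding** says that participants, outcome assessor and statistician are blinded and that the surgeon cannot be.
- **Data collection sheet** has women guess their arm "before revealing this information to them at the final visit". **Follow-up** adds: "All measurements at baseline and follow-up visits will be performed by the same researcher".

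**The concern.** A sealed opaque envelope conceals an allocation only if the envelopes of both arms are alike in the hand. Here one arm's envelope holds two ampules and the other, as described, holds only an instruction. The article thus specifies a procedure that works against its own concealment statement and against its own rule that the arm becomes known at opening.

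What is at stake is anything that can still change before opening: the date, the operator, or whether the woman stays in the trial. If such changes depend on the arm, the groups that reach surgery and follow-up may no longer be comparable. Several outcomes are graded by an assessor or by the woman on 3-point scales, so the trial has reason to guard against avoidable bias.

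Two lesser features could add to the leak. The block size is fixed and published, in a single hospital whose surgeons learn each arm. Each woman's arm is also disclosed at her own final visit, while other women are still to be measured.

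**Working it through.** The plan gives no figure on this point, and the sample size of 150 is not affected. The main step is a comparison of sections; the only arithmetic concerns the blocks.

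**1. Can the envelopes be told apart?**
- Intervention envelope: instruction plus two 1 ml ampules (Randomisation; Procedures).
- Control envelope: instruction. No dummy ampules, padding or rigid container is described.
- The stated property is opacity, which does not mask weight or shape. That the arm can be felt is an inference, but a strong one.

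**2. When, and by whom?**
- Consent comes before randomisation, and opening is on the day of surgery. The exposed period lies between them.
- The only people named as handling an envelope are the independent researcher and, on the day, the surgeon. With those two alone, the exposure runs from collection to opening.
- It is longer if others can reach the cabinet. The article does not say who holds the key, or whether the drug is added in advance or one participant at a time.

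**3. How predictable are fixed blocks of 10?**

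Inputs: 5 + 5 per block and 150 women, hence 15 blocks. Suppose that someone knows every earlier allocation in the block and always guesses the arm with more places left.
- Expected correct guesses per block: 5 + (2^10 / C(10,5) − 1)/2 = 5 + (1024/252 − 1)/2 = 6.53 of 10, or 65% against 50% by chance.
- Allocations known with certainty per block: 10/(5 + 1) = 1.67; over 15 blocks, 25 women.

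This is an upper bound, because allocations are revealed only at surgery whereas women are recruited at around 36 weeks. The article gives no interval between the two, so I assume 2 to 3 weeks. Recruitment from May 2019 to June 2021 is about 25 months, and 150/25 = 6 women a month. About three or four recent allocations would then still be sealed when the next woman is enrolled. Enumerating all 252 possible blocks gives:

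| Most recent allocations still sealed | Correct guesses of 10 | Known with certainty, of 150 |
|---|---|---|
| 0 | 6.53 | 25 |
| 1 | 6.03 | 10 |
| 3 | 5.59 | 0.8 |
| 4 | 5.44 | 0.1 |

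**4. Does disclosure overlap with measurement?**

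The first women recruited in May 2019 reach their 12-month visit about mid-2020, and recruitment is planned to continue to June 2021. Disclosures therefore begin while many women are still to be assessed. The assessor is given randomisation numbers but not arms. If the assessor heard the disclosures, they would be informative about other women in the same block. The article does not say who discloses the arm.

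**The case against.** The strongest defence is that concealment concerns whether those who enrol can foresee the assignment. Here eligibility and consent come first. Randomisation is then done by someone outside theatre and clinic, and the envelope is sealed and locked away. The wording about women already randomised to triamcinolone reads most naturally as adding the drug per participant, in which case no filled envelope exists for a woman not yet enrolled. The surgeon who feels it on the day is unblinded anyway and opens it soon afterwards, the operator is whoever is rostered, and the intention-to-treat analysis keeps postponed women in their arm.

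Most of this stands, and it limits the size of the problem. It does not remove it. The list and the lock protect the sequence but not an envelope in someone's hand, and the article itself intends knowledge of the arm to start at opening. Intention-to-treat also cannot restore outcomes for women withdrawn before surgery.

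Two stronger readings are tempting and are not supported.
- A reader might infer that allocation concealment is absent altogether, with up to all allocations knowable before a woman is approached. That needs envelopes filled ahead of consent and recruiters with access to them; the article shows neither.
- A reader might infer that assessor blinding fails. Ampules felt in the medication room do not inform the assessor, and nothing says that the assessor is present when the arm is disclosed. Scar length and width are also measured by caliper, not graded by eye.

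**Conclusion.** The point holds in a limited form. As described, the two arms' envelopes differ physically, so concealment is not secured from randomisation to opening. It is weakened, not abolished. This rests on the inference that two ampules can be felt and on the absence of any described matching content for controls.

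The effect on the results cannot be put into a number from the article. It depends on who handles the envelopes and on whether schedules, operators or withdrawals then change. Block predictability is a secondary matter: 65% correct guesses and 25 women known with certainty are ceilings that require every earlier allocation to be known at enrolment. Under the assumed 2 to 3 weeks to surgery, the figures fall to about 54% to 56% and to no more than about one woman. A fixed block of 10 is not in itself an error. Disclosure at each woman's own final visit is an avoidable risk to assessor blinding, not a demonstrated breach.

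This should be fixed because the remedy is cheap, but it does not undermine the trial as designed.

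**What to change.** **Main change.** Use identical paper-only envelopes in both arms. Keep the drug separately and release it after the envelope has been opened in theatre. State in the protocol when envelopes are prepared and who has access to the cabinet. Cost: repacking the unused envelopes, and someone fetches the drug after opening.

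**Secondary protections.**
- For the unused part of the list, use varying block sizes that are not disclosed to site staff. Cost: regenerating that part of the list.
- Either defer disclosure of the arm until the last woman's 12-month assessment, or have someone other than the outcome assessor make it, out of the assessor's hearing. The question about which arm she thinks she was in can stay at the final visit. Cost: with deferral, women wait longer to learn their arm; otherwise, a second staff member at that visit.

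None of these changes affects the treatment, the sample size or the analysis.
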